# Protocol for a randomised, double-blind trial of a chronotherapeutic mobile health (mHealth) behaviour change intervention to optimise light exposure among older adults aged ≥ 60 years in Singapore (LightSPAN)

**DOI:** 10.1186/s12877-026-07105-6

**Published:** 2026-02-25

**Keywords:** Digital health, Older adults, Chronobiology, Behaviour change, Light exposure

## Abstract

**Background:**

Suboptimal light exposure among older adults can exacerbate circadian disruption, sleep disturbances, mood disorders, cognitive decline, and frailty. In urbanised environments like Singapore, older adults are particularly vulnerable due to lifestyle and built environment constraints. The LightSPAN study evaluates a chronotherapeutic mobile health (mHealth) behaviour change intervention, delivered via the LightUP app, designed to optimise light exposure patterns and support healthy ageing.

**Methods:**

The trial is a community-based, double-blind, parallel-group randomised controlled trial involving approximately 90 community-dwelling older adults (≥ 60 years) recruited through Active Ageing Centres in Singapore. Participants will be randomised using a secure web-based system with stratification by age, sex and recruitment site to receive either the active LightUP app with behaviour change features (goal setting, self-monitoring, personalised feedback) or a placebo version without these features. The primary outcome is daily time above 250 lx melanopic equivalent daylight illuminance (melanopic EDI) during daytime, measured with the ActLumus light logger across baseline, intervention and follow-up periods. Secondary outcomes include sleep parameters and circadian rest-activity rhythms, sleep quality, mood, cognition, frailty status, physical activity, body composition and vitamin D levels. The usability and acceptability of the LightUP app and wearable devices will also be assessed. Analyses will follow the intention-to-treat principle, supplemented by per-protocol analyses. Generalised linear mixed models will be used for repeated measures, with multiple imputation for missing data and exploratory Bayesian analyses. All analyses will be pre-registered on the Open Science Framework and de-identified datasets and code will be openly shared under a CC-BY license.

**Discussion:**

Despite its central role in circadian regulation, light exposure has rarely been targeted in behavioural preventive interventions for older adults. This study evaluates a novel mHealth-enabled approach that empowers older adults to optimise their light exposure, extending the scope of non-pharmacological strategies for preventive medicine and health promotion.

**Trial registration:**

This study was retrospectively registered at the ISRCTN – The UK’s Clinical Study Registry on 05 September 2025 (ID: ISRCTN12391932, 10.1186/ISRCTN12391932).

**Supplementary Information:**

The online version contains supplementary material available at 10.1186/s12877-026-07105-6.

## Background

Light is the primary zeitgeber for the human circadian clocks, regulating sleep-wake timing, physiology and health [1]. Inadequate or poorly timed light exposure is associated with circadian disruption, impaired sleep, mood disturbances, cognitive decline and metabolic dysregulation [2–4]. Older adults are particularly vulnerable, as ageing is associated with reduced ocular light transmission, decreased outdoor activity and comorbidities that reduce daily light exposure [5–11].

Evidence suggests that improving light exposure can stabilise circadian rhythms and support sleep and wellbeing in ageing populations, including patients with dementia [12–14]. However, conventional interventions such as bright light therapy boxes, while effective in controlled trials, often face barriers to real-world use: they require active engagement, can be costly and show low adherence [15]. Recent work has highlighted the need for scalable, accessible and user-friendly strategies that deliver sustained behavioural change in light exposure [16].

Mobile health (mHealth) interventions offer a promising alternative. Smartphones can provide personalised feedback, encourage self-monitoring and deliver behaviour change techniques. While mHealth approaches have been widely studied for physical activity, diet and chronic disease management, little evidence exists on their role in modifying light exposure behaviour [16, 17]. Integrating wearable light sensors with mHealth interventions could provide a scalable, data-driven solution to optimise daily light exposure in naturalistic settings.

The LightSPAN study evaluates a chronotherapeutic, mHealth-enabled behaviour change intervention aimed at optimising daily light exposure patterns and supporting circadian health, to facilitate and promote healthy ageing among community-dwelling older adults in Singapore.

## Methods

### Objectives

The general objective of this protocol is to evaluate the effectiveness of the LightSPAN mHealth intervention in optimising light exposure behaviour and improving physiological outcomes among community-dwelling older adults in Singapore.

The specific objectives are:

To assess the effectiveness of the LightUP app in optimising daily light exposure patternsTo determine whether the intervention improves circadian rest-activity rhythms, sleep quantity and quality, mood and cognitive performanceTo evaluate effects on frailty status, physical activity, body composition and vitamin D statusTo examine feasibility, acceptability, usability and user satisfaction of the interventionTo explore the acceptability and user experience of the ActLumus light logger device

### Study design

The LightSPAN trial is a randomised, double-blind, parallel-group, placebo-controlled trial conducted among community-dwelling older adults in Singapore. The trial is conducted at Lions Befrienders Active Ageing Centres across Singapore, which serve as community hubs for older adults.

Following eligibility screening and informed consent, participants undergo a 4-week baseline observation period during which habitual light exposure, sleep, and activity patterns are monitored using wearable devices. Participants are then randomised in a 1:1 ratio to either the intervention arm, which receives the LightUP app with active behaviour change features, or the control arm, which receives a placebo version of the app without behavioural components. The intervention period lasts 12 weeks and is followed by a 12-week post-intervention follow-up period, including a 2-week monitoring phase. Study staff conducting outcome assessments are blinded to group allocation throughout the study.

All assessments and app-based interventions are coordinated by TUMCREATE. Participants are expected to attend assessments at the respective Active Ageing Centres, while the intervention itself is delivered in participants’ home environments using smartphones and wearable devices. Participating Active Ageing Centres provide accessible facilities for participant recruitment and assessment. Personnel involved in delivering the intervention and conducting assessments are trained research staff with specific expertise in cognitive, mood, frailty, and physical performance testing, ensuring consistency and quality in data collection.

The trial design therefore allows for evaluation of both short-term (during intervention) and sustained (post-intervention) effects on light exposure, circadian rhythms, sleep, mood, cognition, frailty, physical activity and vitamin D status. This protocol adheres to the Standard Protocol Items: Recommendations for Interventional Trials (SPIRIT) 2025 guidelines to ensure complete and transparent reporting [18].

### Public involvement

Members of the public were involved in the design and planning of this study. Feedback from older adults recruited through community partners in Singapore helped to shape the study aims, ensure the intervention content was accessible and adapt the study procedures for cultural and linguistic appropriateness. Input was obtained on the usability of the mHealth app, the acceptability of wearing devices (light logger and activity tracker) and the burden of participant assessments. Community organisations and social service agencies such as Lions Befrienders also contributed to the development of recruitment strategies at Active Ageing Centres and will assist in the dissemination of study findings to participants and the wider community. The process of obtaining feedback from older adults and community partners has been reported in the published co-design protocol [19]. Participants and public representatives were not involved in drafting the present protocol.

### Participants

Participants are community-dwelling older adults aged 60 years and above, residing in Singapore. At the screening visit, participants provide sociodemographic and background information using structured questionnaires. This includes age, sex, highest level of education completed, occupational history, marital status, living arrangement, and smartphone ownership and use, including the smartphone model used during the study. Health history and comorbidity status are assessed using the Self-Administered Comorbidity Questionnaire (SCQ) [20]. Additionally, we will administer the Morningness-Eveningness Questionnaire (MEQ) [21] and the Munich ChronoType Questionnaire (MCTQ) [22] to assess participants' chronotypes. These screening data are collected to describe the study sample and to support secondary and exploratory analyses examining factors that may influence adherence and intervention outcomes. Eligibility criteria are outlined below.

#### Eligibility criteria

Participants must be capable of independent mobility, with or without assistive devices and demonstrate functional independence as assessed by the Lawton Instrumental Activities of Daily Living (IADL) scale [23], with a score greater than 8 for females and greater than 5 for males. Participants are required to own a smartphone, be proficient in English reading and communication and not be currently enrolled in another mHealth interventional study.

Exclusion criteria include the presence of cognitive impairment, defined as a Montreal Cognitive Assessment (MoCA) [24] score below 26 after education adjustment, or depressive symptoms, defined as a score greater than 6 on the short form of the Geriatric Depression Scale (GDS) [25]. Individuals with significant physical impairments and/or medical diagnoses that interfere with daily activities, severe terminal illness, or psychiatric conditions affecting daily function will be excluded. Participants with visual impairment, diagnosed eye diseases, ocular abnormalities (as assessed by a licensed optometrist), or uncorrected hearing impairment are not eligible.

### Recruitment, randomization, blinding and treatment allocation

#### Recruitment

Participants will be recruited from Lions Befrienders Active Ageing Centres across Singapore, which provide access to a diverse population of community-dwelling older adults. Recruitment strategies include on-site information sessions, flyers and outreach via community staff. Interested individuals will be screened for eligibility by trained research staff.

Enrolment will continue until the target sample size of 90 participants is reached. Research staff will maintain regular contact with participants during the baseline monitoring period to encourage retention and to address technical issues promptly. The collaboration with established community organisations is expected to facilitate efficient recruitment and reduce participant burden.

#### Randomisation

##### Sequence generation

Randomisation will be conducted using computer-generated block randomisation with the R package *blockTools*, stratified by age, sex and recruitment location to ensure balanced allocation across key demographic variables.

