#### Primary outcome analysis

The primary endpoint is light exposure behaviour, operationalised as the mean daily time (minutes per day) spent above 250 lx melanopic EDI during daytime hours. Light exposure patterns will be analysed per individual using generalised linear mixed models (GLMMs). Daily TAT values will be entered into models including group assignment and assessment block/day-in-trial as fixed effects, with participant-level random effects to account for repeated daily measurements.

Based on prior analyses of TAT in a Malaysia–Switzerland light exposure study [34], Poisson and Gamma error distributions were identified as an appropriate fit for mixed-effects modelling and are therefore used for all analyses with TAT as the dependent variable.

The full model in Wilkinson notation will follow this specification:$$\begin{aligned}&\:\mathrm{Outcome\:variable}\:\sim\:\mathrm{group}*\mathrm{assessment\:block}\\&+\mathrm{sex}+\mathrm{age}+\left(\mathrm{assessment\:block}\right|\mathrm{participant})\:\end{aligned}$$

Model diagnostics will include visual checks for homoscedasticity, normality of residuals and random effects, and their location at zero. Baseline characteristics, including sociodemographic variables, health status, and baseline outcome measures, will be summarised descriptively by study group, and selected variables may be included as covariates in secondary or exploratory analyses where appropriate.

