## Discussion

### Strengths

This study has several strengths. It represents a novel digital behavioural intervention that specifically targets environmental light exposure as a modifiable, lifestyle-based strategy for preventive health and health promotion among older adults. To our knowledge, this is the first study to operationalise light exposure optimisation through a mHealth platform in this population. The trial is underpinned by a rigorous methodological design, employing a double-blind randomised controlled framework with allocation concealment and stratified balancing by sex, age, and recruitment site. These design features minimise selection and performance bias and enhance internal validity. A further strength is the use of a multi-modal assessment framework that combines objective measures of light exposure, physical activity, and physiological outcomes, captured using the ActLumus light logger and Garmin Vivosmart 5, with validated subjective instruments. This approach enables comprehensive outcome assessment and robust triangulation across measurement modalities. The inclusion of a pilot and feasibility phase allows refinement of study procedures, identification of implementation challenges, and optimisation of intervention delivery prior to the trial, thereby reducing operational risks and strengthening overall feasibility. Finally, recruitment through Lions Befrienders’ Active Ageing Centres situates the intervention within a real-world community context, enhancing ecological validity and supporting the potential translation of findings into community-based and public health programmes.

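### Recruitment site is a stratification factor but is absent from the full primary model; the cost is a possibly conservative test and a forgone gain in power, not bias

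*Protocol article*

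**What the plan says.** Three places in the protocol article name the same three balancing factors. Sequence generation describes block randomisation "stratified by age, sex and recruitment location to ensure balanced allocation across key demographic variables". The abstract's Methods paragraph refers to "stratification by age, sex and recruitment site". The Strengths section counts "stratified balancing by sex, age, and recruitment site" among the features that support internal validity. There is more than one centre: "Participants will be recruited from Lions Befrienders Active Ageing Centres across Singapore". The number of centres is not stated.

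Under Primary outcome analysis the article introduces its formula with "The full model in Wilkinson notation will follow this specification". The terms are group, assessment block and their interaction, then sex, age, and a random assessment-block effect by participant. The text of the same section describes the random part as "with participant-level random effects to account for repeated daily measurements". Site appears as neither a fixed nor a random term. The only latitude on covariates is that "selected variables may be included as covariates in secondary or exploratory analyses where appropriate", which does not reach the primary analysis.

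Secondary outcomes analyses lists group, block, their interaction and a participant random effect, and names no stratification factor.

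**The concern.** When allocation is balanced within the levels of a factor, differences between those levels no longer add to the sampling variance of the treatment contrast. A model without the factor still counts that variance in its residual or participant-level terms. The standard error is then larger than the design warrants, and the test rejects too rarely under the null. Keeping two stratification factors and dropping the third, without a reason, leaves the analysis out of step with the randomisation.

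What is at stake is precision that the stratification makes available and the model does not collect. Site could plausibly matter here, since the abstract's Background points to lifestyle and built-environment constraints, and these can differ between neighbourhoods. The documents offer no data on how much it matters.

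**Working it through.** **1. Compare the lists.** Stratification factors: age, sex, site. Covariates in the full primary model: age, sex. The difference is site.

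**2. The plan's own figure.** Sample size gives 25 per group for 80% power at two-sided 5%, from a simulation with a mixed model containing intervention and a participant random effect. A closed formula cannot reproduce that simulation, and this point does not depend on it. What matters is that the power model has no site term, so the natural reading is that the 80% refers to total variance. On the normal scale, 80% power corresponds to a standardised effect of 1.96 + 0.84 = 2.80.

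**3. Which variance counts.** The treatment effect is the group-by-block interaction, that is, a difference between groups in change from baseline. A site difference that is constant over time is taken up by the participant intercepts and the baseline block and drops out of this contrast. Only site differences in the *change* matter. Call their share of the variance of the change s; the documents give no value, so 2-15% is assumed.

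**4. Formulas.** Stratification removes the share s from the true variance of the contrast, while the model without site still estimates the total.

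- Type I error without site: 2 × [1 − Φ(1.96/√(1−s))]
- Power without site: Φ((2.80 − 1.96)/√(1−s))
- Power with site: Φ(2.80/√(1−s) − 1.96)

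| s (assumed) | √(1−s) | critical value in true SE units | type I error without site | power without site | power with site |
|---|---|---|---|---|---|
| 0.02 | 0.990 | 1.980 | 4.8% | 80.2% | 80.8% |
| 0.05 | 0.975 | 2.011 | 4.4% | 80.6% | 82.0% |
| 0.10 | 0.949 | 2.066 | 3.9% | 81.2% | 84.0% |
| 0.15 | 0.922 | 2.126 | 3.4% | 81.9% | 86.0% |

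With site in the model, type I error is 5% in every row. The formulas ignore the degrees of freedom that site terms use.

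**5. Simulation check.** Setting: 90 participants, 5 centres (assumed), 1:1 allocation balanced within centre, normally distributed change from baseline, 6000 runs per setting.

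| Site share of variance of change | type I error without site | type I error with site |
|---|---|---|
| 0 (site affects level only) | 5.5% | 5.4% |
| 0.10 | 3.8% | 4.9% |
| 0.20 | 3.2% | 5.1% |

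The 10% row agrees with the formula. The first row confirms that a pure level difference has next to no effect. Both checks use a normal approximation rather than the planned Poisson or Gamma mixed model, so the sizes are illustrative.

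**The case against.** A reader might infer that the omission pulls the trial below its planned power. The calculation behind that reading is Φ(2.80 − 1.96/√(1−s)), which gives 79% at s = 0.02 and 75% at s = 0.15. It requires the planned 80% to have been computed on variance already net of site. Sample size describes no such step, and its power model has no site term. On total variance the unadjusted test stays at about 80-82%. Nor do the 31-34 expected completers per group make matters worse, since the plan needs only 25 per group. Even on that pessimistic formula with s = 0.15, scaling 2.80 by √(31/25) and √(34/25) gives about 84-87%.

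A second tempting inference is that the standard errors are certainly too large. They are so only if site affects the change over time. The documents do not show this, and Study design says that the intervention is delivered in participants' homes. Sex and age also enter as main effects only, so much of their contribution cancels from the interaction as well.

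It can also be said that a separate analysis plan is announced. For the primary model this does not answer the point, because the article sets out the full formula rather than deferring it. For the secondary models the objection has weight: they are not labelled complete, and optional covariates are allowed there. That part is an alignment to make at the same time, not a separate defect.

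**Conclusion.** The mismatch is certain from the text: site is used to randomise and is missing from the primary model that the article fixes. Its consequence is modest and conditional. There is no bias and no excess of false positives. Under the assumed 2-15% share of the variance of change, the test is somewhat conservative and about 0.6 to 4 percentage points of attainable power go unused (80.8 − 80.2 at the low end, 86.0 − 81.9 at the high end). If centres differ only in their level of light exposure, the loss on the group-by-block test is close to nil. The documents do not support a claim that power falls short of the planned 80%. The size rests on the assumed site share, on reading the 80% as referring to total variance, and on a normal approximation. The correction is inexpensive and worth making before the analysis plan is finalised.

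**What to change.** Add recruitment site to the primary model in the categories used for stratification, and add site, age and sex to the secondary models. Two forms are reasonable:

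- a random site intercept, with a site-by-block component if it can be estimated; or
- if centres are few, a fixed site effect, with small centres pooled by a rule set in advance.

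The site-by-block component is the part that can recover precision for the group-by-block contrast, since a site main effect alone largely cancels from it. If site is to stay out, the plan should say why.

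Sample size and data collection do not change. The cost is extra parameters, and it depends on the form. With 9 centres and 3 blocks (both assumed), fixed site and site-by-block terms add 8 + 8 × 2 = 24 parameters, which is heavy for 63-68 completers in a model that already has random block effects. With many centres the random form is therefore the more practical choice.

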##### Allocation concealment and implementation

To guarantee allocation concealment, the allocation sequence will be securely implemented by a research team member who is not in direct contact with the participants.

Participant enrolment is conducted by trained research staff at the partner Active Ageing Centres. Group assignment is performed only after eligibility confirmation and completion of the baseline observation phase. The random allocation sequence is generated by an independent statistician and stored within a secure, central, web-based randomisation module managed by the data management team. Enrolling staff request assignment through this system; the system releases the allocation only at the point of randomisation. Personnel responsible for enrolment and those delivering study procedures have no access to the randomisation list or block details. The master sequence file is access-restricted (statistician and data manager only) and kept on an encrypted server with audit logs.

